## Abstract

**Background:**

Vessel-sparing anastomotic repair (vsAR) has been developed as a less traumatic alternative to transecting anastomotic repair (tAR) to treat isolated short bulbar urethral strictures. This vessel-sparing technique could result in improved functional outcomes without jeopardizing the excellent surgical outcome after (transecting) anastomotic repair. The purpose of this study is to directly compare vsAR and tAR for both surgical and functional outcomes.

**Methods:**

This trial is a prospective, interventional, multi-center, single-blinded, 1:1 randomized, controlled, non-inferiority, phase II trial. Sample size calculation resulted in a required sample size of 100 patients (50 patients per arm). Trial participants will be randomized by an independent third party using a computer-based random sequence generator with permuted blocks of variable size. The primary objective of this trial is to show that vsAR is non-inferior to tAR in terms of failure-free survival after 24 months of follow-up, considering a non-inferiority limit of 10%. Failure is defined as the inability to pass a 16-Fr flexible cystoscope through the reconstructed area without damaging the urethral mucosa. Secondary end-points mainly include differences in postoperative complications and changes in functional outcome parameters, which will be assessed with validated questionnaires. All participants are scheduled for follow-up at 3, 12, and 24 months postoperatively.

**Discussion:**

This trial will provide level Ib evidence about the differences in both surgical and functional outcome between vsAR and tAR, which may importantly scape the future of bulbar urethral reconstruction. Depending on the trial results, this phase II trial may generate a larger phase III trial with more statistical power and a lower alpha value.

**Trial registration:**

This trial is registered at clinicaltrials.gov (NCT03572348) and in the Belgian Clinical Trial Registry (B670201837335). The trial was registered prospectively. Registered on 28 June 2018.

## Administrative information

Note: the numbers in curly brackets in this protocol refer to SPIRIT checklist item numbers. The order of the items has been modified to group similar items (see http://www.equator-network.org/reporting-guidelines/spirit-2013-statement-defining-standard-protocol-items-for-clinical-trials/).

## Introduction

### Background and rationale {6a}

Urethral stricture disease is a common urological condition in men. Although rigorous epidemiologic data are sparse, the existing papers report an incidence varying between 0.6 and 1.4% [1]. Urethral strictures can occur throughout the entire length of the urethra, but mainly involve the anterior urethra and in particular the bulbar segment [2].

The International Consultation on Urologic Diseases (ICUD) recommends anastomotic repair (AR) urethroplasty for isolated short bulbar urethral strictures [3]. This approach, in which the diseased bulbar urethral segment is excised and an end-to-end anastomosis is performed, is an optimal choice for strictures up to 3 cm and provides a composite success rate of 93.8% [3].

Traditionally, AR urethroplasty involved full thickness transection of the corpus spongiosum and the embedded urethral blood supply. However, it is only required to excise the narrow segment of the urethra and the surrounding spongiofibrosis, and therefore, a full thickness transection of the corpus spongiosum is in fact unnecessary. Against this background, Jordan et al. published an alternative, vessel-sparing technique in 2007 [4, 5], and since then, several urethroplasty centers have implemented this technique in their surgical repertoire [6–10]. It should be noted though that in some of these centers the vessel-sparing technique does not involve an active dissection and isolation of the bulbar arteries at the bulb of the corpus spongiosum, in contrast to Jordan et al., as this dissection is in fact unnecessary, time-consuming, and more traumatizing [6, 7].

Anyhow, the act of leaving the bulbar arteries intact in vessel-sparing anastomotic repair (vsAR) could offer certain functional benefits compared to the classic transecting anastomotic repair (tAR) technique. Preserving the bulbar arteries potentially reduces the risk of postoperative erectile dysfunction or glans ischemia, and it could be beneficial for subsequent interventions of the urethra; a free graft urethroplasty for instance, in which a rich vascular bed is essential; or the implantation of an artificial urinary sphincter, in which a well-sustained vascularization is imperative for success [4–7]. However, prospective studies comparing the functional outcome of both techniques with validated questionnaires are currently lacking, and thus, these potential benefits remain mere theoretical assumptions.

Be that as it may and potential functional benefits aside, vsAR should at least be able to provide a comparable (or non-inferior) surgical success rate as the transecting technique to be considered a truly valuable alternative. Promising short-term results have been described in single-arm observational studies and are in line with the reported composite success rate of the ICUD [3, 6–10]. However, direct comparisons between vsAR and tAR have only been done in retrospective studies which are strongly biased by the fact that patients who underwent vsAR had shorter follow-up than patients who underwent tAR [11, 12]. Moreover, since vsAR is a more novel technique, one could hypothesize that the performing surgeon is better trained and more experienced in the era of vsAR compared to the earlier in their surgical career, when tAR was the only AR technique.

Considering the above, the aim of this randomized controlled trial is to directly compare vsAR and tAR for both surgical and functional outcomes.

## Objectives {7}

The primary objective of this trial is to show that failure-free survival (FFS) after vsAR is non-inferior to tAR after 24 months of follow-up.

❖ Failure is defined as the inability to pass a 16-Fr flexible cystoscope through the reconstructed area without damaging the urethral mucosa.

❖ The non-inferiority limit, *d*, was set at 10%. This non-inferiority limit was chosen based on experts’ opinion, 5 patients’ opinion, and a round-the-table consensus discussion.

❖ The fact that failure after AR usually occurs within the first years after surgery serves as the rationale behind the follow-up interval of 24 months in this study [13].

Main research question, study hypothesis (Ha), and null hypothesis (H0) based on primary objective:
Is the FFS after vsAR not inferior to the FFS after tAR in isolated short bulbar urethral strictures?Study hypothesis (Ha): The FFS after vsAR is not inferior to the FFS after tAR in isolated short bulbar urethral strictures.Null hypothesis (H0): The FFS after vsAR is inferior to the FFS after tAR in isolated short bulbar urethral strictures.

## Trial design {8}

This trial is a prospective, interventional, multi-center, single-blinded, 1:1 randomized, controlled, non-inferiority, phase II trial.

### Eligibility criteria {10}

Inclusion criteria for participants:
Voluntarily signed written informed consent according to the rules of ICH-GCP (Declaration of Helsinki) and national regulations.Age ≥ 18 years.Male patient.Fit for operation, based on the surgeon’s expert opinion.Isolated short (≤ 3 cm) bulbar urethral stricture confirmed by imaging. Imaging includes at least retrograde urethrography (RUG). In case of equivocal findings, voiding cysto-urethrography (VCUG) and urethroscopy must be added.Patient is able and willing to comply with the postoperative protocol.

Exclusion criteria for participants:
Absence of signed written informed consent.Age < 18 years.Female patients.Transgender patients.Patients unfit for operation.Concomitant urethral strictures at other urethral locations (penile urethra, membranous urethra, prostatic urethra, bladder neck).Urethral strictures > 3 cm.Urethral stricture(s) at other urethral locations (penile urethra, membranous urethra, prostatic urethra, bladder neck).Lichen sclerosus-related strictures.Strictures after failed hypospadias repair.Patients with neurogenic bladder.Shift of technique to augmented urethroplasty or any technique other than AR due to any circumstance. These patients will be logged, but will be excluded (post-hoc) from further analysis within this trial.History of pelvic radiation therapy.Active treatment to enhance erectile function (such as PDE5-inhibitors and intracavernous injections) at the moment of prescreening for inclusion in this trial.Any condition or situation, which, in the investigator’s opinion, puts the patient at significant risk, could confound the study results, or may interfere significantly with the patient’s participation in the study.Patient declares that it will be impossible for him to attend the follow-up consultations.

Eligibility criteria for participating centers:

Only urethral surgeons who state that they are sufficiently capable of performing both vsAR and tAR are allowed to participate in this trial.

### Who will take informed consent? {26a}

Patients meeting the in- and exclusion criteria of this trial will be thoroughly informed about this trial by the local principal investigator (PI) and will be asked if they are willing to participate. If so, the local PI will ask the patient to sign the written informed consent form. All informed consent forms will be stored in a locked file cabinet, unavailable to anyone except the local PI.

### Additional consent provisions for collection and use of participant data and biological specimens {26b}

Not applicable as no biological specimens will be collected as part of this trial.

## Interventions

### Explanation for the choice of comparators {6b}

The comparator, tAR, has been the gold standard technique for as long as anastomotic repairs exist [3]. In 2007, vsAR was invented as a less traumatic variant of the classic tAR, hoping to optimize functional outcome after this procedure without jeopardizing the excellent FFS rates after this type of surgery [4, 5].

### Intervention description {11a}

All patients will be asked to sign the written informed consent form at the beginning of the study, and once signed, they will be asked to fill in the preoperative questionnaire.

Preoperatively, all patients will be asked to deliver a urine sample for urinalysis and urine culture. Patients with evidence of a urinary tract infection will be treated with adequate antibiotics according to the participating center’s standard of care.

The same routine perioperative care will be applied to patients of both groups.

Surgical approach will be different for patients of different groups:
Main steps in vsAR involve: midline perineal skin incision, cleavage of the bulbospongious muscle, circumferential dissection of the bulbar urethra, mobilization of the urethra by freeing it circumferentially from the penoscrotal angle up to the urogenital diaphragm, dorsal longitudinal urethrotomy over the strictured area, resection of the urethral stricture and surrounding spongiofibrosis, dorsal spatulation of the healthy urethral ends, transverse closure of the urethra over a catheter, spongioplasty, closure of the bulbospongious muscle, and closure of the wound in multiple layers [14].Main steps in tAR involve: midline perineal skin incision, cleavage of the bulbospongious muscle, circumferential dissection of the bulbar urethra, mobilization of the urethra by freeing it circumferentially from the penoscrotal angle up to the urogenital diaphragm, resecting the entire urethral segment (with its surrounding corpus spongiosum) that is strictured, spatulation of the healthy urethral ends, transverse closure of the urethra over a catheter, spongioplasty, closure of the bulbospongious muscle and closure of the wound in multiple layers.

As mentioned above, routine postoperative care will be provided to all patients and will be similar for patients of both groups.

A voiding cysto-urethrography (VCUG) will be performed 10–14 days after surgery, and in case of no or insignificant contrast leakage, the transurethral catheter will be removed. In case of significant contrast extravasation, the catheter will be maintained and imaging will be repeated 1 week later until no more significant contrast leakage can be identified. This short-term imaging will be similar for patients of both groups.

Follow-up moments will be held at 3, 12, and 24 months postoperatively and will involve urethroscopy, filling in the postoperative questionnaire and uroflowmetry. Follow-up will be similar for patients of both groups.

### Criteria for discontinuing or modifying allocated interventions {11b}

Conversion of vsAR to tAR for any reason is allowed upon the operating surgeon’s discretion. These patients will be considered part of the vsAR group in the intention-to-treat (ITT) analyses and will be considered part of the tAR group in the per-protocol (PP) analyses.

All shifts of technique towards augmented urethroplasty or any technique other than AR due to any circumstance will be logged, but these patients will be excluded (post-hoc) from further analysis within this trial.

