In every scenario, the power was set at 0.80, according to the guidelines for designing a phase II trial [21]. The results for different alphas are displayed above. Usually, a non-inferiority trial demands a significance level, alpha, of 0.025 as these trials only look at one boundary of the classic two-sided 95% confidence interval (CI) [22]. However, these conditions often lead to (sometimes unreasonably) high sample size calculations requiring excessive financing and recruitment. As a solution, researchers often design a phase II trial that allows for more coincidence and thus a trial with a higher significance level, alpha. Rubinstein et al. reported alpha values of 0.10 and 0.20 to be allowed in a phase II trial [21]. Considering the fact that a non-inferiority trial relies on one-sided testing, we believe a one-sided significance level, alpha, of 0.10 is allowed and most feasible.

Considering all of the above, a scenario in which the power is set at 0.80, the one-sided significance level, alpha, is set at 0.10, the estimated success in control group is set at 95.4%, and the estimated success in experimental group is set at 95.3% was found most realistic and feasible. Considering this and accounting for a realistic drop-out of 20% (experience based), it was estimated that each arm has to consist of 50 patients, resulting in a total sample size of 100 patients.

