### Concealment mechanism {16b}

Random allocation of patients to one of both treatment arms will be done by a third party who is further not involved in any process of the trial. When a participating center other than Ghent University Hospital wants to allocate a patient to one of both treatment arms, the local PI will contact the third party for randomization within 1 week before the planned operation (by central telephone number or e-mail address) and will ask to which treatment arm “patient X who is going to be operated on dd/mm/yyyy” is allocated. Note that there will be no communication of names, initials, or birth dates of patients; only pseudonymized data will be transferred. After receival of this request for randomization of a patient, the third party for randomization will assign a unique trial identifier to the patient at hand and will respond to which treatment arm this patient has been allocated.

As such, the randomization process is concealed for the treating surgeon up until 1 week before surgery. Since these two different techniques may entail different operating room preparations (different retractors, different sutures, etc.), randomization concealment for the treating surgeon is lifted 1 week preoperatively for logistic considerations.

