## Assignment of interventions: blinding

### Who will be blinded {17a}

Trial participants will be blinded and, as mentioned above, randomization of patients will be concealed for the treating surgeon up until 1 week preoperatively.

Blinding of outcome assessors and data analysts was considered, but we decided against this due to practical considerations.

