## Statistical methods

### Statistical methods for primary and secondary outcomes {20a}

ITT analyses will be used for all end-points.

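### Men whose operation shifts to a non-anastomotic technique are excluded after randomisation, which contradicts the ITT analysis promised for all end-points and opens the primary comparison to bias of unknown direction and size

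*Protocol article*

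**What the plan says.** All references are to the protocol article.

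- Eligibility criteria {10} lists this among the exclusion criteria: "Shift of technique to augmented urethroplasty or any technique other than AR due to any circumstance". It adds that such men are logged and left out of the analysis.
- Criteria for discontinuing or modifying allocated interventions {11b} repeats the rule: "these patients will be excluded (post-hoc) from further analysis within this trial".
- The same section handles a conversion from vsAR to tAR differently: "These patients will be considered part of the vsAR group in the intention-to-treat (ITT) analyses". Those men move to the tAR group only for per-protocol analyses.
- Statistical methods for primary and secondary outcomes {20a} states, without exception or modified-ITT label: "ITT analyses will be used for all end-points".
- On timing, Concealment mechanism {16b} says for centres other than Ghent University Hospital that "the local PI will contact the third party for randomization within 1 week before the planned operation". It says more generally that "randomization concealment for the treating surgeon is lifted 1 week preoperatively for logistic considerations".
- Who will be blinded {17a} adds: "Blinding of outcome assessors and data analysts was considered, but we decided against this due to practical considerations".

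**The concern.** An exclusion criterion should describe a man as he is before randomisation. A shift away from the allocated technique is an event after randomisation, so listing it under eligibility does not make it a baseline criterion. Removing men for it means that the groups compared are no longer the groups randomised, and the analysis is not the ITT analysis that the plan names.

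The rule covers any reason, sets no objective trigger, and operates when the surgeon knows the arm. Under Outcomes {12} the protocol rejects re-intervention as an end-point because a physician's preference for one technique could distort it. The same reasoning applies to a decision that takes a man out of the analysis.

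The trial expects very few failures, so a handful of exclusions could matter to the non-inferiority conclusion. Shifts are logged, but no analysis that retains these men is described. The only per-protocol analysis described (Methods for additional analyses {20b}) concerns erectile function, so nothing stated would show the effect on the primary end-point.

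**Working it through.** **1. The text side by side.** Section {20a} applies ITT to all end-points. Section {11b} keeps one kind of departure from the allocated technique (vsAR to tAR) in the randomised arm and deletes another (AR to non-AR). Both follow randomisation. The second cannot be reconciled with section {20a} as written.

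**2. The plan's own figure.** Sample size {14} uses tAR success 95.4%, vsAR success 95.3%, margin 10 points, power 0.80, and on alpha says "we believe a one-sided significance level, alpha, of 0.10 is allowed and most feasible". With unpooled variance:

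n = (1.2816 + 0.8416)² × (0.954 × 0.046 + 0.953 × 0.047) / (0.10 − 0.001)² = 4.508 × 0.08868 / 0.009801 = 40.8, so 41 per arm, as stated.

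**3. Expected failures.** 50 × 0.046 = 2.3 in tAR and 50 × 0.047 = 2.35 in vsAR.

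**4. How far exclusion moves one arm's failure proportion.** Let k of 50 vsAR men be shifted, with failure rate f, and let the others fail at 4.7%. Retained, the arm's failure proportion is [k·f + (50 − k) × 0.047] / 50. Excluded, it is 0.047. The difference is (k/50)(f − 0.047). The values of k and f are assumptions; the protocol gives neither.

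- k = 2, f = 0.20: 0.04 × 0.153 = 0.6 points
- k = 2, f = 0.40: 0.04 × 0.353 = 1.4 points
- k = 5, f = 0.20: 0.10 × 0.153 = 1.5 points
- k = 5, f = 0.40: 0.10 × 0.353 = 3.5 points

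If the same shifts fell only in tAR, (k/50)(f − 0.046) gives 0.6 to 3.5 points the other way. The sign depends on which arm loses more men and how they fare.

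**5. Effect on the decision rule.** Take 50 men per arm, 2 failures per arm among AR patients, two shifts in vsAR, none in tAR, and a normal approximation for the 80% interval.

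- Excluded: 46/48 − 48/50 = −0.2 points; SE 0.0400; lower limit −0.0017 − 1.2816 × 0.0400 = −5.3%. Non-inferior.
- Retained, one fails: 47/50 − 48/50 = −2.0 points; SE 0.0435; lower limit −7.6%. Non-inferior.
- Retained, both fail (worst case): 46/50 − 48/50 = −4.0 points; SE 0.0473; lower limit −10.07%. Non-inferiority lost.

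**6. Effect on the false-positive rate.** Put the true ITT difference at the margin (95.4% against 85.4%), with 40 evaluable men per arm before exclusions and a share q shifted in vsAR only. Success among the remaining vsAR men is s = [0.854 − q(1 − f)] / (1 − q), on 40(1 − q) men. The chance of concluding non-inferiority is Φ[(s − 0.854)/SE − 1.2816], nominally 10%.

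- f = 30%: 11.8% at q = 4% and 15.4% at q = 10%.
- f = 100%: 24.4% at q = 4% and 73.8% at q = 10%.

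**The case against.** The strongest reply is that the rule is prespecified, stated twice, applied to both arms, and accompanied by logging. It stands directly after the ITT and per-protocol definitions, so the planned set can be read as a modified ITT population of men who received AR. That makes the rule transparent. It does not make it ITT, and section {20a} carries no such qualification. Relabelling would cure the contradiction but not the possible bias.

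A shift might also reveal that a man was never eligible. An exclusion limited to that case could be defended, but the rule has no such limit.

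Three further points stand against a stronger claim.

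- A reader might infer that the rule rewards vsAR by removing strictures that cannot be repaired without transection. The text does not support this. Such a man would convert to tAR, which is AR, and would stay in the vsAR arm. Incision, dissection and mobilisation are common to both arms (Intervention description {11a}), and nothing in the protocol shows that AR is abandoned more often in one arm.
- A reader might infer that the exclusions leave the trial materially short of patients. The protocol does not say whether its experience-based 20% drop-out allowance covers these men. Power also falls slowly: 80.2% at 41 per arm, 79.4% at 40 and 77.9% at 38.
- The most striking figures in steps 5 and 6 require every shifted man to fail and every shift to fall in vsAR. At 30% failure the inflation is modest. Equal shifts with equal outcomes in both arms would give little bias.

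That the shift happens during the operation, and that the surgeon decides it, is inferred. The text says only that technique shifts. The timing of randomisation and the word post-hoc place it after randomisation, which is all the argument needs.

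**Conclusion.** The point holds as a contradiction in the analysis population and an unprotected primary comparison. Sections {10} and {11b} remove randomised men for an event after randomisation, while section {20a} promises ITT for everything. With the surgeon aware of the allocation, and assessors and analysts unblinded, balance between the exclusions cannot be assumed.

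Bias is possible, not shown. If all shifts fall in vsAR and step 4's assumptions hold, exclusion makes vsAR look better by about 0.6 to 3.5 points, at most about a third of the margin (3.5/10). If they fall in tAR, it makes vsAR look worse by a similar amount. A reader might conclude that the rule favours non-inferiority, but the protocol gives no basis for a direction. Two patients could reverse the conclusion, though only in the worst case of step 5.

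**What to change.** - Delete the technique-shift item from the exclusion criteria in section {10} and the matching exclusion sentence in section {11b}.
- State that every randomised man is analysed in his allocated arm for the primary ITT analysis, using the 3-, 12- and 24-month visits and the same 16-Fr cystoscope end-point. That end-point refers to the reconstructed area, so it can also be applied after a non-AR urethroplasty.
- Report the number of shifts, with reasons, by arm.
- Present the AR-only set as a named sensitivity analysis.

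The cost is an amendment and the follow-up of a few more men. The protocol removes them from analysis but does not say that their follow-up stops, and it describes trial follow-up as comparable to routine follow-up. The estimate becomes slightly less specific to AR, which the sensitivity analysis covers. No stated sample-size figure changes.
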